**5. A description of the stopping rules for individuals, parts of trial and entire trial**

The clinical investigator will evaluate the local and systemic adverse reactions of each subject. If a subject experiences serious unexpected local or systemic adverse reactions then this will be reported in PANVAK according to national guidelines from the Norwegian Institute for Public Health.

**6. Maintenance of trial treatment codes and procedures for breaking the codes.**

This study is an open study but the serological samples will be coded for laboratory analysis.

**7. The identification of any data to be recorded directly in CRFs and to be considered to be source data**

The study data will be verifiable to the source data, which necessitates access to all original recordings, such as subject list, blood sample log, vaccine administration log and adverse event forms. A daily log will be kept of all events related to the trial. On the day of vaccination, each subject in the immunogenicity study will be randomly allocated a unique subject identification number in order to protect confidentiality. The original source documentation will be a paper-based database, which will include the original hard copy of the results from the computer database (referred to below) of the serological results, and other information related to clinical trial. All databases will be secured against unauthorised access and confidentiality will be

maintained at all times. One paper database will be held at the immunisation clinic at the hospital and will contain personal data (name, sex, age, contact details, next of kin, and the National Personal Identification Number (personal number)). The vaccination records will be stored in the National Institute for Public Health database (PANVAK) for pandemic vaccines with only the relevant Haukeland University Hospital staff having access to this database, by use of his/her personal access code to the hospital database. A paper database of adverse event forms will be kept at the Centre for Infection Control and these will be code with a unique number before the side reactions are entered into a computer database. The second database will be laboratory-based and contain the subject identification number and data relating to immunological responses, the only personal data will be age, sex and previous influenza history. The sponsor or her nominee will only have access to this database and it will be secured against unauthorised access.

## **6 Selection and Withdrawal of subjects**

### **1. Subjects inclusion criteria**

The following subjects will be considered eligible to enter the study or receive the second dose of vaccine if the following criteria are met:

#### Inclusion criteria

- Signed informed consent
- Subjects able to understand and comply with the study protocol and complete the Adverse Event Form
- Subjects able to attend the scheduled visits for the immunogenicity and kinetic study

### **2. Subjects exclusion criteria**

The following subjects will not be considered eligible to enter the study:

- Persons with a history of anaphylaxis or serious reactions to any vaccine
- Person with known hypersensitivity to any of the vaccine components
- Persons who have had a temperature  $>38^{\circ}\text{C}$  during the previous 72 hours
- Persons who have had an acute respiratory infection during the last 7 days
- Suspected non-compliance

### **3. Subjects withdrawal criteria**

#### When and how to withdraw subjects from the trial

The clinical investigator will evaluate the local and systemic adverse reactions of each subject. If a subject experiences unexpected serious local or systemic reactions then these will be recorded in SYSVAK according to the national guidelines.

#### The type and timing of data to be collected for withdrawn subjects

No further trial samples will be collected from subjects who withdraw their informed consent for their participation in the study.

#### Whether and how subjects are to be replaced

Subjects will not be replaced if they are withdrawn or voluntarily withdraw from the trial.

#### The follow-up for subjects withdrawn from treatment

This study will gather information on the safety, tolerability and immunogenicity of the pandemic A/H1N1 vaccine administered as part of the mass vaccination campaign. As no treatment is given directly in this study there will be no follow up of subjects, however, subjects will be followed by Haukeland University Hospital when deemed clinically necessary.

## **7. Treatment of Subjects**

### **1. Treatment to be administered including name of all products, the doses, the dosing schedule, the route of administration and the treatment periods including follow-up periods for the subjects for each product treatment group.**

Subjects will receive one dose of pandemic A/H1N1 influenza vaccine by intramuscular injection into the deltoid muscle, as part of the mass vaccination campaign recommended by the Norwegian Institute for Public Health. Each subject will be enrolled in the study for 6 weeks for the adverse events and for 2 years for the immunogenicity study. They will be involved in the trial for a period of 6 weeks, during which blood samples will be collected at days 0, 7, 14 and 21 days after

pH11N and seasonal vaccination. All subjects will be asked to voluntarily provide trial blood samples at 3, 6, 12, 18 and 24 months after pH11N and seasonal vaccination to examine the longevity of the antibody response.

## **2. Medication permitted (including rescue medication) and not permitted before and /or during trial**

All subjects enrolled in this trial may continue their normal medication throughout the study. Subjects may continue to take therapy for chronic medical conditions, but must be maintained on a stable regimen for at least 2 weeks prior to study entry as assessed by their Medical History.

If anaphylactic shock occurs after vaccination, it will be treated according to the standard routines at Haukeland University Hospital using hydrocortisone sodium succinate (Solu-Cortef 100mg), dexchlorfeniramine (5mg/mL), atropine (1mg/ml), adrenaline (1mg/mL and 0.1mg/mL). Use of other medication including over-the-counter products will be discouraged during the study. Investigational drugs are prohibited during the course of the study.

## **3. Procedures for monitoring subject compliance**

This study is a vaccine study and forms part of the hospitals mass vaccination campaign. For subjects involved in the immunogenicity and kinetic studies, the daily log of events and CRF will be used to record if subjects have been vaccinated and provided the appropriate trial samples. All subjects vaccinated will be recorded in the PANVAK database according to the national guidelines.

# **8 Assessment of Efficacy**

## **1. Specification of efficacy parameters**

In the absence of true efficacy markers like prevention of illness and/or reduction of morbidity and mortality, serum anti-HA antibodies are the most commonly measured correlate of protection against influenza (65) or surrogates of efficacy. The CHMP have defined criteria for the annual update for seasonal influenza vaccines, which measure the serological responses by the haemagglutination inhibition or single radial haemolysis assays. An HI titre  $\geq 40$  (or an equivalent

SRH > 25mm^2) indicates 50% protective levels of serum antibody against influenza infection in man. The EU evaluation criteria in groups of at least 50 adults aged 18-60 approximately at 3 weeks after vaccination are:

- The number of seroconversions or significant increases in anti-haemagglutinin antibody titre should be > 40%;
- Mean geometric increase >2.5;
- The proportion of subjects achieving an HI titre  $\geq 40$  or SRH > 25mm^2 should be >70%

The CHMP require for marketing authorisation of a pandemic vaccine that the vaccine fulfils all current evaluation criteria for seasonal vaccines despite the immunological naivety of the host. The serological responses of vaccinees in the immunogenicity study will be evaluated and the ability of the vaccine to meet the CHMP criteria at different time points after vaccination will be determined.

In a pandemic situation, it is important to know how rapidly the immune response is elicited after vaccination with a novel subtype (60). Thus, the detailed kinetics of the immune response in immunologically naïve individuals will also be assessed through the induction of local and systemic antibody and cellular immune responses and results will be compared to published results on the response to current influenza vaccines in healthy adults. Furthermore, there is a clear need for improved understanding of the immune response elicited in human volunteers including the quality and repertoire of the antibody response which will be evaluated by ELISA and phage display, respectively. Two other important factors are the capacity of the vaccine to elicit long lasting immunity and cross reactive immunity to H1N1 influenza viruses (60). These will be evaluated by the standard serological assays and through the induction of local antibody and systemic cellular immune responses.

## **2. Methods and timing for assessing recording and analyzing efficacy parameters**

In the immunogenicity study, blood samples will be taken for serological assays at days 0, 7, 14 and 21 after pH1N and seasonal vaccination. This study is an open study but all sera will be coded and blinded assays will be conducted by the University of Bergen, the National Institute of Biological Standards and Control, Health Protection Agency and University of Sienna, (SRH, HI, and neutralisation assays) on samples collected up to 21 ± 4 days after vaccination. When these

serological assays are completed the immunogenicity of the A/H1N1 influenza vaccine will then be assessed according to the three evaluation criteria defined by the CHMP and the following will be calculated:

- The number of subjects who seroconvert or show significant increases in anti-haemagglutinin antibody titre;
- The mean geometric increase;
- The proportion of subjects achieving an HI titre  $\geq 40$  or SRH  $> 25\text{mm}^2$ .

The immunogenicity of the vaccine will also be evaluated by

- Producing a detailed time course of the immune response to vaccination including the kinetics of the T, B- and serum antibody responses
- The ability of the vaccine to induce long lasting immunity using the blood samples collected at 6, 12, 18 and 24 months after pandemic and seasonal vaccination.
- The ability of the vaccine to induce cross-reactive immunity to other H1N1 strains.
- Examining the quality and repertoire of the antibody response.

#### Deviation from protocol

The investigators will adhere and try to avoid deviations from the protocol. The clinical investigators will document and explain any deviations from the approved protocol. Blood sampling for kinetic studies (T, B and antibody) can be collected within the following time frames after both the first and second doses of vaccine - day  $0 \pm 0$ ,  $7 \pm 2$ ,  $14 \pm 2$ ,  $21 \pm 4$ . Subjects who do not adhere to these sampling time points have deviated from the protocol and their inclusion in the comparative serological analyses will be evaluated by the investigators.

#### Protocol amendments

The sponsor will treat any protocol amendments according to European guideline “Detailed guidance for the request for authorisation of a clinical trial on a medicinal product for human use to the competent authorities, notification of substantial amendments and declaration of the end of the trial”. The regulatory authorities will be notified about substantial amendments and these amendments must be approved before being implemented.

## 9 Assessment of Safety

One of the main aims of this study is to evaluate the occurrence of adverse events in people vaccinated with the pandemic A/H1N1 vaccine. All subjects will be asked to fill in the adverse events form to record the incidence of local and systemic solicited side reactions. All adverse events and their follow up will be recorded in SYSVAK according to the national guidelines.

### a. Adverse events (AE)

Note that the term vaccine refers to the pandemic A/H1N1 influenza vaccine in this study.

#### Definitions

##### **Adverse events**

An AE is any untoward medical occurrence in a patient or subject which does not necessarily have a causal relationship with a medical treatment. This includes any noxious, pathological or unintended change in anatomical, physiological, or metabolic functions as indicated by physical signs, symptoms and/or laboratory-detected changes. These might occur in any phase of the clinical study whether associated with or related to the vaccine or not. This includes also exacerbations of pre-existing conditions or events, intercurrent illnesses, or vaccine- or drug interactions. Anticipated day-to-day fluctuations of pre-existing conditions that do not represent a clinically significant exacerbation are not considered AEs. Discrete episodes of chronic conditions occurring during a study period should be reported as AE in order to assess changes in frequency or severity.

##### **Serious adverse events (SAE)**

SAEs are a subset of AEs. A SAE is defined as any untoward medical occurrence or effect at any dose that

- results in **death**
- is **life-threatening**: i.e. the subject was at risk of death at the time of the event; it does not refer to an event which hypothetically might have caused death if it were more severe
- results in persistent or significant **disability/incapacity**: i.e. results in a substantial disruption of the subject's ability to carry out normal life functions.
- requires in-patient **hospitalisation** or prolongation of existing hospitalisation: i.e. the subject is detained (usually at least an overnight stay) at the hospital or emergency ward for treatment that would not have been appropriate in the physician's office or in an out-patient setting. Hospitalisation for either elective surgery related to a pre-existing

condition which did not increase in severity or frequency following initiation of the study or for routine clinical procedures (including hospitalisation for "social" reasons) that are not the result of an AE are **not** considered as SAEs

- is a **congenital anomaly or birth defect** in the offspring of a study subject
- is an **important medical event** that may jeopardise the subject or may require intervention to prevent one of the other outcomes listed above: e.g. interventions such as intensive treatment in an emergency room or at home for allergic bronchospasm; blood dyscrasias or convulsions that do not result in hospitalization, or development of drug dependency or drug abuse. Based on medical and scientific judgment, these events should usually be considered serious

Although **not** considered as SAE, cancer should be reported in the same way as SAEs.

Note: If anything untoward is reported during an elective procedure, that occurrence must be reported as an AE, either serious or non-serious according to the criteria defined above. When in doubt as to whether hospitalisation occurred or was necessary, the AE should be considered serious.

#### Surveillance, reporting, and documentation of adverse events

The recording of AEs is an essential part of study documentation. The clinical investigator is responsible for documenting all AEs as set out in the following sections.

#### Documentation of solicited adverse events

Solicited AEs are precisely defined events that the subjects are specifically asked about and which are documented by the subjects in the adverse event form. This form will be the source document.

The following local AEs at the vaccine injection site (injections site reactions) will be documented in the Adverse Event Form:

- Pain
- Erythema
- Ecchymosis
- Induration
- Itching
- Swelling

---

 A procedure which may take place during the study period and should not interfere with the vaccine administration or any of the ongoing protocol-specific procedures.

The following solicited systemic AEs will be documented in the adverse event form and transcribed by the investigator into the CRF:

- Body temperature (oral)  $\geq 38^{\circ}\text{C}$
- Malaise
- Shivering
- Fatigue
- Headache
- Sweating
- Myalgia
- Arthralgia
- Diarrhoea
- Respiratory symptoms

An Adverse Event Form will be issued to all subjects instructing them to record their daily local and systemic adverse events for as long as symptoms persist. The subjects will provide information on the presence or absence of solicited local and systemic adverse events. The use of antipyretic/relief medication and any changes in medication will also be recorded. Subjects will score the severity of symptoms as follows:

Blank – no adverse symptoms

1 -symptom occurred but not severe enough to cause inconvenience

2 -symptom occurred severe enough to interfere with daily activities but required minimal or no medical intervention

3-symptom occurred severe enough to markedly interfere with daily activities; required medical consultation

At each visit for the immunogenicity study, all AEs, either observed by the clinical investigator or his nominee or reported by the subjects spontaneously or in response to a direct question will be evaluated by the investigator.

As a consistent method to find out about adverse events, the investigator should use a non-leading question, such as:

"Have you felt different since receiving the vaccine or since the previous visit?"

The subjects will be instructed to contact the clinical investigators immediately should they experience any signs or symptoms they perceive as serious during the period extending from the first study-specific procedure up to and including 6 months (minimum 180 days) after the last administration of the vaccine.

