## **5 TRIAL DESIGN**

### **1. A specific statement of the primary endpoints and secondary endpoints to be measured by the trial**

The primary endpoints of the trial are the local and systemic adverse events and tolerability of parenterally administered adjuvanted H1N1 influenza vaccine in all volunteers. The secondary

endpoints are the evaluation of the immunogenicity of adjuvanted H1N1 influenza vaccine and the ability of the vaccine to meet the CHMP evaluation criteria in a subset of volunteers.

The immunogenicity of the H1N1 vaccine will be assessed through the induction of specific local and systemic antibody and cellular immune responses, and analyses of the epitopes to which the response is directed. Furthermore, the capacity of the vaccine to elicit cross reactive and long lasting immunity will be evaluated. In a pandemic situation, an important aspect is the rapidity of the immune response to the H1N1 vaccine and therefore the detailed kinetics of the immune response will be investigated.

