## **STUDY PROCEDURE FOR SUBJECTS IN THE IMMUNOGENICITY AND KINETIC STUDIES**

### First visit: Day 0: First vaccination

Subjects will be enrolled following one to one interviews for immunogenicity and kinetic studies providing they meet inclusion and not meeting the exclusion criteria and give fully signed informed consent. The following procedures will then be carried out and recorded in the Case Report Form:

- Record personal details including age, sex, personal number
- Record relevant medical and medication history;
- Record influenza vaccination history;
- Allocate a unique subject identification number;
- Trial blood samples will be collected by venepuncture to measure the antibody, T- and B-cellular and antibody responses.
- An Orasure fluid sample will be collected to measure the local antibody response. The oral fluid sample will be collected using an absorbent pad placed on the gum to absorb the oral fluid for two minutes.
- Subjects meeting the inclusion and not meeting the exclusion criteria will be vaccinated parenterally (into the deltoid muscle of the upper arm (the opposite side to that used for venepuncture)). Vaccination will be recorded in PANVAK according to National guidelines. The side of injection will be recorded in the CRF
- Subjects will be observed for 30 minutes to check for immediate adverse reactions. Emergency equipment (adrenaline, corticosteroids) will be available in the event of a rare anaphylactic reaction to vaccine administration.
- The vaccination site will be examined for local reactions at the end of 30 minutes. These findings and any systemic adverse reactions will be recorded on the appropriate CRF page.
- Dispense the subject's adverse event forms to the subjects, and give instructions for its completion. The adverse event form must be returned to the site at the Day 21 visit.
- Each subject will be instructed in the evaluation of local and systemic adverse events.
- Schedule the next clinic visit.

Second visit: Day 7 ( $\pm 2$  day) post 1st vaccination

- The adverse event form will be reviewed.
- Trial blood samples will be collected by venepuncture to measure the antibody, T- and B-cellular and antibody responses.
- An Orasure fluid sample will be collected to measure the local antibody response.
- Schedule the next clinic visit.

Third visit: Day 14 ( $\pm 2$  days) post 1st vaccination

- The adverse event form will be reviewed.

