### Severity of adverse events

The severity of unsolicited AEs will be graded on a 3-point scale as follows:

| Grade        | Definition                                                                                                                                                                               |
|--------------|------------------------------------------------------------------------------------------------------------------------------------------------------------------------------------------|
| 1 (mild)     | Discomfort noted, but no disruption of normal daily activity; slightly bothersome; relieved with or without symptomatic treatment.                                                       |
| 2 (moderate) | Discomfort sufficient to reduce or affect normal daily activity to some degree; bothersome; interferes with normal daily activities; only partially relieved with symptomatic treatment. |
| 3 (severe)   | Discomfort sufficient to reduce or affect normal daily activity considerably; prevents regular activities; not relieved with symptomatic treatment.                                      |

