## **2. The number of subjects planned to be enrolled and reason for choice of sample size**

All subjects included for mass vaccination will be included in the adverse events analysis which should provide a database containing a maximum of 8000 reports. The CHMP criteria for licensure of seasonal vaccines require data from 50 volunteers and this number has been chosen as the subset of volunteers to be included in the kinetic study. Up to 500 subjects willing to provide three blood samples will be included in the immunogenicity studies.

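### The adverse event form scores a blank as no symptom, so a skipped item on a returned form is recorded as symptom-free and solicited reaction rates can only be biased downward

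*Protocol*

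**What the plan says.** Section 5.1 of the protocol states: "The primary endpoints of the trial are the local and systemic adverse events and tolerability" of the vaccine in all volunteers. Section 9 (Documentation of solicited adverse events) lists the local and systemic symptoms on the adverse event form and says of it: "This form will be the source document". It also says: "The subjects will provide information on the presence or absence of solicited local and systemic adverse events". The scoring key that follows has four levels: "Blank – no adverse symptoms", then 1, 2 and 3. It has no zero, no box for an absent symptom and no code for an unanswered item.

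On the analysis set, section 10.2 says: "All subjects included for mass vaccination will be included in the adverse events analysis". The same sentence describes the result as a database of at most 8000 reports. Section 10.1 speaks of up to 8000 volunteers.

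On retrieving the form, the first-visit procedure for the immunogenicity and kinetic studies says: "The adverse event form must be returned to the site at the Day 21 visit". In those studies the form is also reviewed at Days 7 and 14 and discussed at Day 21, and section 9 adds a direct question at each visit. No comparable step is described for subjects who are only in the adverse reactions study.

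**The concern.** Two different facts produce the same entry. A subject who had no headache leaves the headache item empty, and so does a subject who had one and overlooked the item. The section promises information on both presence and absence, yet absence can be shown only by writing nothing.

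The error runs one way: a blank can turn a symptom into no symptom, but never the reverse. It falls on the solicited part of the primary endpoint, and a large sample does not reduce it. Several thousand reports give a narrow interval around a value that is too low.

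The coding also weakens the protocol's own controls. Section 14 makes the investigators responsible for complete forms, and section 12 requires a check that entries are correct and complete. Where an empty item is a valid answer, the completeness of the symptom items cannot be checked.

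This is not a matter left to a statistical analysis plan. Such a plan can choose a denominator, but it cannot recover an answer that the form never captured.

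**Working it through.** **Inputs**

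- Number of reports: at most 8000 (section 10.2). It is a ceiling that matches the approximate number of hospital employees in section 2.4. No precision or power calculation is given for safety, so there is no planned figure to reproduce.
- True rate of a solicited reaction, p: assumed to be 50%. The protocol's background section on the safety of inactivated influenza vaccine puts mild local reactions at more than half of healthy adults.
- Share of symptomatic subjects who leave the item blank, s: not stated. Assumed range 2% to 10%.

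**Item rate among returned forms**

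Observed rate = p × (1 − s).

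| s | Observed rate | Bias (points) |
|---|---|---|
| 2% | 0.50 × 0.98 = 49.0% | −1.0 |
| 5% | 0.50 × 0.95 = 47.5% | −2.5 |
| 10% | 0.50 × 0.90 = 45.0% | −5.0 |

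**Sampling error for comparison**

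95% half-width = 1.96 × √(p(1 − p)/n).

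- n = 8000: 1.96 × √(0.25/8000) = 1.1 points.
- n = 4000: 1.96 × √(0.25/4000) = 1.5 points.

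The bias equals the half-width when s = half-width/p. That is 0.011/0.50 = 2.2% at 8000 reports and 0.0155/0.50 = 3.1% at 4000. Above these skip rates, the interval would be expected to be centred more than one half-width below the true rate.

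**Where the protocol limits the error**

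- Review, discussion and direct questioning at visits apply only to the immunogenicity subset: up to 550 subjects in section 10.1, up to 500 in section 10.2.
- The form is a daily record kept while symptoms last, so an item is lost only if it stays blank on every affected day. This argues for the lower part of the assumed range.
- The arithmetic is per item. A rate of any local or any systemic reaction falls only if all of a subject's symptomatic items in that group are blank.

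**Severity wording**

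Grade 1 stops below the point of inconvenience, and grade 2 starts where daily activity is affected. A symptom that is inconvenient but does not affect activity fits neither. Grade 3 on this scale reads "symptom occurred severe enough to markedly interfere with daily activities; required medical consultation". Grade 3 for unsolicited events (Severity of adverse events) ends "prevents regular activities; not relieved with symptomatic treatment". The second condition differs between the scales, so one reaction could be graded differently on each.

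**The case against.** The strongest defence is that the effect is unquantified and may be small. The skip rates are assumptions, the form is kept daily, and in the subset with visits the investigator asks directly. All of that stands. It limits the size of the effect, not its direction, and it does nothing for skipped items on forms from subjects without visits.

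A reader might go further and infer from "All subjects included for mass vaccination will be included in the adverse events analysis" that unreturned forms are also counted as symptom-free. The documents do not support that. The blank code applies to items on a form that exists. The same sentence in section 10.2 counts reports, and section 5.7 has reactions entered from coded paper forms, so an unreturned form gives no record. Section 5.7 also says the forms are kept at the Centre for Infection Control, so collection is envisaged even though no return route is described outside the subset. The denominator is ambiguous, and a statistical analysis plan could settle it.

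Nor is the direction of bias from non-return fixed. Take a true rate of 50% and returned forms as the denominator. If 80% of reactors and 50% of others return forms, the rate reads 0.40/(0.40 + 0.25) = 61.5%. If 50% of reactors and 70% of others do, it reads 0.25/(0.25 + 0.35) = 41.7%. If return is unrelated to symptoms, it stays at 50%. These return rates are assumptions too.

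A reader might also infer that a marked reaction without a consultation has no grade. It fits grade 2, which covers interference needing little or no medical intervention, so it is graded lower rather than lost. The unsolicited scale is no model of grading by interference alone, because its grade 3 carries a further condition about relief.

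**Conclusion.** The concern holds for skipped items on returned forms. The coding makes a missing answer and a true absence identical in the source document, and item-level reaction rates can only be lowered by it. The amount is unknown. With an assumed true rate of 50% and 2% to 10% of symptomatic items left blank, the loss is 1 to 5 points, against a half-width of about 1.1 points at the maximum of 8000 reports. At 2% the bias is about the size of sampling error; from 5% it clearly exceeds it. The visit procedures mitigate this only for the immunogenicity subset.

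For unreturned forms, the most that can be said is that section 10.2 is unclear between all subjects and reports. No figure for bias from non-return, and no direction, follows from the protocol.

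The gap between grades 1 and 2 is real but secondary. It affects the distribution of severity more than the count of reactions.

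**What to change.** 1. Add a box **0 = symptom absent** to every solicited item and treat a blank as missing.
2. State in section 10.2 that the denominator for each item is returned forms with that item answered. Report the return rate against the register of vaccinations (section 7.3).
3. For forms already collected under the present key, state that blanks cannot be separated from absence and that the rates are lower bounds with respect to skipped items. This may apply to the main safety data: the background section describes the Bergen vaccination in the past tense with a 2010 reference, and Table 5.1 refers to an extension of the trial. A revised form would then help only with later use.
4. Make the wording of grades 1 and 2 contiguous. Medical consultation can be recorded as a separate yes/no item. Reconcile the solicited and unsolicited severity scales so that their grade 3 definitions can be compared.

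The cost is one form revision and a paragraph of text. The downside is a slightly longer form and a stated return rate that may look less favourable.
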